**Figure 2 figure2:**
[figure not shown]
Sample size formula for two population means.

To factor in 20% attrition, if (n) is the sample size required as per formula and (d) is the dropout rate, adjusted sample size N new is obtained as N1=n/(1–d) [84]. Therefore, the total required per group after adjusted for dropout rate is N1=209/(1–0.2)=261; hence, a total of 522 new international postgraduate students will be needed for the sample size in both groups.

### Intervention

#### Intervention Development

The intervention is developed based on the acculturation and acculturative stress models integrating with a cognitive behavioral theory with the aim of focusing on cross-cultural sessions and social and behavioral issues in order to improve social and psychological adjustment and reduce acculturative stress and intention to drop out among international students, especially those who have just arrived at the new hosting environment. Most of these models highlight important variables, including acculturation experience, acculturation strategies, and social support, which have an effect on decreasing acculturative stress and a positive impact on the adjustment of students in host cultures [68,85,86]. Therefore, this study developed an intervention that targets individual variables such as acculturation, social support, and coping strategies, as these factors have the potential to mitigate acculturative stress and, consequently, the international students’ adjustment and intention to drop out.

The educational intervention was developed based on previous experimental studies on the implementation of intervention programs such as Excellence in Experiential Learning and Leadership developed by Mak et al [87], a cultural transition course for international students by Brunsting et al [88], a behavioral intervention to improve cross-cultural relationships consistent with the acculturation models developed by Pritchard and Skinner [89], a cognitive behavioral group intervention on acculturation by Pan et al [90], a group psychological intervention to enhance coping and acculturating by Smith and Khawaja [91], and further intervention and support programs aiming to improve international students’ sociocultural and psychological adjustment and reduce their acculturative stress and intention to drop out of the university [92-94]. Taking into consideration the limitations of these previous intervention studies, development of the intervention in this study is based on the creative use of cross-cultural activities in a program, using a clear quantitative evaluation of the effectiveness of the program and including components that directly target international students’ psychological and sociocultural adjustment and acculturative stress. The intervention was also developed based on the results of previous studies.

Berry’s model [68] for acculturation places an emphasis on individuals’ cognitive appraisal of acculturative life changes as another factor that has an impact on acculturation. For instance, a given person is likely to appraise a life change as a chance or, alternately, as a stressor that is conducive to acculturative stress. Berry’s model provides a clear picture of the instance or case in which a person appraises a life change as a stressor. Moreover, they may make an additional appraisal of the sufficient coping resources that they have in order to overcome the stressor. Thus, acculturative stress will become low when a person possesses adequate coping resources. As a result, they will be able to psychologically and socioculturally adjust to the new host country. Therefore, the model adopted in this study guides development of the intervention (identifying the necessary components of what an efficient intervention that reduces acculturative stress and improves adjustment should be). These are cognitive appraisals of acculturative life changes, acculturation experience, stressors, acculturative stress, and coping strategies including social support [95]. To achieve this, the study adopts a cognitive behavioral framework for acculturation and acculturative stress since it suits the purpose of this effective intervention. The framework addresses cognitive appraisals and increases coping resources in the cognitive and behavioral domains.

#### Intervention Content

The proposed program will cover a period of 7 sessions and will be conducted over a period of 9 hours in each university of the intervention group. Core modules of the Acculturative Stress Educational Intervention Program will include (1) introduction to the intervention program, (2) introduction to Malaysia and Malaysian culture and customs, (3) study abroad in Malaysia, (4) understanding acculturation, (5) acculturative stress, (6) coping strategies, and (7) adjustment strategies. In each session, participating international students will be offered different topics with experiential and interactive methods of delivery and materials. Websites; videos; demonstrations; in-group activities and interaction; interchanging of cultural background, experience, and intracultural communication; and critical incidents with analysis, reflection, and discussion on different cases and scenarios of international students’ experience with acculturative stress and adjustment will be used for enabling students to engage with the program.

#### Intervention Implementation

The aim of the intervention program is to transfer knowledge and gain skills, and the program will cover two parts: (1) a seminar session with PowerPoint (Microsoft Corp) presentation covering the 7 sessions, providing knowledge about different aspects of Malaysia and Malaysian culture, acculturation, and acculturation strategies and (2) knowledge and activities will be provided about acculturative stress, the sources for acculturative stress, adjustment, coping strategies, and social support. In this part, group exercises and activities will be used for enabling the students to engage with the program and gain knowledge and skills. Therefore, the intervention program will be delivered through seminar sessions, a PowerPoint presentation, videos, group activities, a printed booklet, and other printed materials that are available on the website during the intervention and study but can be accessed only by the intervention group using codes. Website, email, and WhatsApp are the primary methods to deliver the educational materials to the intervention group. These technological tools will be used to send short reminder messages and encourage participants to take part in the intervention and control groups. Participants in the study will be provided useful information about the topic and how to cope and adjust in the new environment. The second phase focuses on participants’ independent processing and implementing of information provided in the first phase as they begin to use the information in their personal lives and develop the skills necessary for enhancing their situation.

### Study Variables and Instruments

This study will use a self-administered questionnaire consisting of 8 sections measuring the sociodemographic, independent, and dependent variables (study outcomes). The questionnaires will be completed at time 1, time 2, and time 3.

#### Primary Outcome: Acculturative Stress

Stress is defined as a state of a person that results from their interaction with their surroundings and is regarded as a threat to the well-being of the individual. Since this study focuses on international students’ acculturative stress as the primary outcome, we conceptualize acculturative stress as stress that a person suffers from reaction or response to stressful events of life relevant to the process of acculturation [65] as well as the psychological difficulties in the new culture [96]. Acculturative stress is also a psychosocial result of the individual’s lacking familiarity with the customs and social norms of the host culture [97,98]. Hence, one of the focuses of the investigation in this study is the acculturative stress experienced by international students in the Malaysian context [99-101].

This study uses the Acculturative Stress Scale for International Students (ASSIS) for measuring the primary outcome, international students’ acculturative stress. The measure is effective in examining international students’ cross-cultural adjustment, specifically the extent to which they find their involvement in everyday social situations as difficult due to cultural differences. ASSIS is widely used in studies on international students’ acculturative stress in Malaysia, and the scale is also highly reliable and valid as reported in early research [29,32,66,101-106]. The overall score for the ASSIS is in the range of 36 to 180. The use of the total score of the ASSIS is highly encouraged by Sandhu and Asrabadi [103]. In the case of using the total scores, high scores mean that the individual’s perceived acculturative stress is high [46,104-106].

#### Secondary Outcomes: Adjustment and Intention to Drop Out

Adjustment is known as a short-term and dynamic process experienced by the individual in relation to the new cultural environment; it also refers to the degree to which a certain university meets the demands or requirements of international students [107-109]. According to Ward and Kennedy [110], there are two dimensions of adjustment: sociocultural and psychological.

First, sociocultural adjustment is a process in which individuals with different cultural backgrounds become skilled and able to engage in negotiating the host culture and effectively interacting with its local people [111]. Assessment of the individual’s sociocultural adaptation is based on a 20-item version of the Sociocultural Adaptation Scale (SCAS) [110]. Participants will be asked questions regarding the degree of difficulty experienced by them in a number of areas [110,112-115]. This is based on a 5-point Likert scale for rating the difficulty of 20 daily situations adapted by the participating international students in the Malaysian context. Initial use of the SCAS was documented in a previous study that indicated it was reliable, with scale alphas ranging from .75 to .91, indicating good internal consistency and construct validity [110-115]. The SCAS is regarded as a flexible research instrument and measure that is easily modified based on characteristics of the sojourning sample, and it can be adapted to different cultural contexts [34].

Second, the Satisfaction with Life Scale (SWLS) is used to measure psychological adjustment and the cognitive component of subjective well-being [116] through 5 items. Consistent with the standpoint of the World Health Organization on health, psychological adjustment is seen as state of well-being and not merely the absence of disease [117]. Hence, its specific focus is on evaluating individuals’ perceived satisfaction with life as a whole based on their criteria and views [118,119]. The items on the SWLS are based on a 5-point scale on which respondents are asked to agree or disagree with 5 statements (eg, “In most ways my life is close to my ideal”). The scale is available in a range of languages and has been used in cross-cultural research [118], and its internal consistency for psychological adjustment has proved to be very good [34,42,109,119].

Finally, the international students’ intention to drop out of the university is also a secondary outcome. This variable describes the international students’ intended behavior concerning their persistence of studies in the host country. It will be measured using this single item: How likely is it that you will withdraw from university (for whatever reason)? This question underlying the dependent variable of students’ intention to drop out is known to be the best predictor of students’ actual behavior and can be used in the absence of behavioral data [120,121]. In our study, this question is intended to seek participating students’ responses to whether they were thinking of or had already thought of dropping out of university.

#### Sociodemographic Information Questionnaire

All participants will be asked to provide sociodemographic information including their gender, age, marital status, educational level, duration of stay in Malaysia, country of origin, prior traveling experience, native language, and self-reported proficiency of language. Self-reported proficiency will also be assessed using a composite score from the following questions: (1) What is your present level of English fluency? (2) How comfortable are you communicating in English? (3) How often do you communicate in English? This method of measuring and assessing English language proficiency has been documented previously by several researchers [122-125]. For this study, participants will be asked to rate their perceived proficiency in speaking, understanding, writing, and having a conversation in Malay and English, as language skills are said to enable sojourners to interact with host nationals and engage in interpersonal relationships, which, in turn, influences their adaptation [125,126].

#### Other Independent Variables and Measurements

This study focuses on other independent variables that directly or indirect affect study outcomes: acculturation, social support, and acculturative stressors.

Acculturation is a process of adaptation or adjustment to a new cultural context that imposes behavioral, cultural, and psychological changes on the individual in an attempt to be in contact with other individuals or even groups coming from diverse cultural backgrounds [65,127]. Participants’ acculturation will be measured using the Acculturation Index (AI) [128]. The AI was adopted from the two-dimensional acculturation model of Berry et al [61]. These two basic dimensions of acculturation are students’ identification with their heritage culture and their relationship with the host culture. The scale comprises 21 cognitive and behavioral items (eg, food, language, recreational activities, social customs, pace of life, religious beliefs). The instrument is intended to identify acculturation strategies used by participants [110,115,128,129]. Participants will be given two questions on their current lifestyles in two cultures: “How similar are your experiences and behaviors to members of your culture of origin?” and “How similar are your experiences and behaviors to members of Malaysian culture?” This instrument makes use of a 5-point, partly anchored, Likert-type scale ranging from 1=not at all similar to 5=very similar. Independent scores for the two dimensions are in the range of 0 and 105, and higher scores are indicative of the participants’ stronger identification with the host culture. In previous studies, internal consistencies and reliabilities were illustrated by Cronbach alphas ranging from .91 to .94 and .89 to .97 for the heritage culture and host culture, respectively. These reliabilities were confirmed by studies using this measure among sojourns from different cultures living in different populations [115,128,129].

While acculturative stressors are those related to international students’ acculturative process at the biological, social, functional, cultural, and physical/environmental levels [130], other related stressors include reentry issues. Acculturative stressors will be measured by the International Student Acculturative Stressor Scale (ISASS) developed by Eustace [131] for the purpose of capturing the degree to which each acculturative stressor represents an issue or difficulty for the international students participating in this study. Respondents will be provided with a 5-point Likert-type scale with 13 items that allow them to rate their degree of difficulty of the different acculturative stressors. The options ranged from 1=not difficult at all to 5=very difficult. The total scores for the 13 items ranged between 13 and 65. Higher scores indicate higher levels of difficulty of such acculturative stressors.

Perceived social support is another dependent variable, defined as the individual’s impression of the available resources that are supportive for them during their experience of stress and symptoms experienced. Social support encompasses three different dimensions: family, friends, and significant others. Whereas family and friends are recognized as self-explanatory, significant others might be a supervisor, peer, colleague, or any other person with whom the stressed person has constant contact [42,132,133]. In this study, the Multidimensional Scale of Perceived Social Support (MSPSS) aims to measure international students’ perceived social support. It was designed and developed by Zimet et al [132] based on adult samples. Several studies have used the MSPSS with the aim of measuring perceived social support across different cultures [119,132,134-136]. It is reported to be a short, clear, and accurate scale that can be used for measuring social support. The MSPSS is also relatively free of the biases of social desirability [137]. Using this scale, respondents select from the 5-point Likert-type scale choices ranging from 1=strongly disagree to 5=strongly agree. In a previous study, the factor loadings of these items were relatively high, and the measure had internal consistencies (Cronbach alphas) of .79, .81, and .82 for family, friend, and significant other support, respectively. In another study in the Malaysian context, internal consistency results were reported of .88, .64, and .87 for family support, friend support, and the availability of a special person [42,109,119].

### Quality Assessment

Prior to distributing the questionnaires to the targets of the study, the researcher conducted a pilot study as recommended by scholars to reduce ambiguity, validate the instrument, and evaluate the educational intervention program before conducting the study [138,139]. For the validation of the intervention module and educational materials, the researcher constructed the basis of each statement, information, guideline, or strategy in the educational module from credible published scientific sources. A panel of experts then engaged in reviewing all sources and the newly developed educational intervention before providing it to the study sample. The experts read the references used in developing the module and educational materials and were asked to provide their evaluation and suggestions for enhancement. This was followed by resending the final module to the panel of experts for a second review. This resulted into the final version of the educational module and educational materials that will be used in this study.

After the educational module and materials were designed, a group of experts in psychiatry and education (3 experts from the psychiatric department, faculty of medicine, and 3 from the faculty of education) rated the content validity of the educational module and materials from the proposed educational intervention in terms of its accuracy, currency, and appropriateness of content using a 5-point scale: 1=extremely unsuitable to 5=extremely suitable. They will be also asked to identify areas of items that need to be improved, removed, or modified [140]; we will then pretest the educational module and materials among new international students in a private university to evaluate the reliability of the educational module and materials.

### Statistical Analysis

We will use SPSS Statistics version 25.0 (IBM Corp) to analyze the data. Statistical significance will be considered as a *P* value of less than .05. Analysis of the data will take into account clustering of students within universities. The study will use statistical analyses, including descriptive statistics of the respondents’ sociodemographic characteristics, chi-square test for nonparametric variables, and 2-tailed *t* test for continuous variables, to compare between the control and intervention groups on sociodemographic variables and primary and secondary outcome measures. Complete case analyses, intent-to-treat analyses, and completer status analyses will be conducted according to the initial allocation of universities to either intervention or control groups. In relation to the missing data, we will follow the guidelines for analyzing and reporting cluster RCTs with missing data established by Fiero et al [141] and Díaz et al [142].

The effectiveness of the intervention will be assessed using the generalized estimation equation (GEE). Specifically, the differences in the research hypothesis in terms of students’ acculturative stress, adjustment (sociocultural and phycological), and intention to drop out will be compared at 3 points—time 1 (preintervention), time 2 (immediately postintervention), and time 3 (3-month follow-up)—between and within the intervention and the control groups adjusted for covariate variables. The GEE method was chosen because of its efficiency in appropriately modeling the structure of the correlations of the pre-post repeated measures and its low degree of reliance on the assumption of normality in the distributions of data for the variables in the analysis. Furthermore, in the context of RCT research, multilevel models such as the GEE are the most appropriate model because they permit the estimation of treatment effects (ie, group differences) across multiple time points within a single statistical model [143].

However, there is no default option in the GEE analysis for eta squared to obtain the intervention effect size that can be expressed as a standardized effect size. Therefore, two popular measures, Cohen d and eta squared, will be used in this study. Cohen d = beta ÷ standard deviation, with beta representing the difference between two means for the two groups relative to their standard deviation obtained from the pooled variance to compute the effect size within group and between group [144-146]. Hence, d = (mean 1 – mean 2) / (the average standard deviation of the two groups). The eta squared indicates how much of the total variance is explained by the difference between the means. Therefore, we will convert the effect size d to eta squared with the equation η^2^=d^2^/d^2+4^. The reported effect size d is also interpreted by Cohen [147] as adopted by many previous studies, specifically intervention as well in terms of the practical or clinical significance of the effect, 0.2 (small effect), 0.5 (moderate effect), and 0.8 (large effect), and similarly for eta squared 0.01 (small effect), 0.06 (moderate effect), and 0.14 (large effect) [146,148-151].

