### Sample Size

The total sample size needed will be calculated by applying the formula for two population means [78] as seen in Figure 2. Means and standard deviation used for the intervention group and control group were based on the estimation offered in a previous RCT [79]: µ1=2.58, µ2=2.07, SD1=1.08, SD2=1.08, n1=24, n2=30. Therefore, the total sample (n) will account for 71 participants. Calculation of the required sample size in this study was performed based on the guidelines in the CONSORT for cluster RCTs [73]. By considering the account intraclass correlation coefficient (ICC), it is necessary to multiply the sample size in RCTs by design effect=1+(m–1)*ICC, where m is the average cluster size [80-83]. Thus, the average class size is assumed to be 40 participating students, and an ICC of .05 could be expected. This would result in design effect N=1+(m–1)*ICC=1+(40–1)*.05=2.95. Based on the sample size required by the formula, the required minimum sample size for each group after adjusting for design effect is n=71*2.95=209, and the total sample size required is 209 participants per arm.

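### The Statistical Analysis section promises to allow for university clustering, then names ordinary t and chi-square tests between arms, outcomes included, that do not allow for it

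*Protocol article*

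**What the plan says.** In the protocol article, Statistical Analysis sets significance at a P "value of less than .05" and then states: "Analysis of the data will take into account clustering of students within universities". The sentence that follows lists descriptive statistics, a chi-square test and a "2-tailed *t* test for continuous variables", and gives their purpose as "to compare between the control and intervention groups on sociodemographic variables and primary and secondary outcome measures". It gives no time point, and it mentions no cluster-level or cluster-adjusted form of either test.

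The next paragraph of the same section assigns the assessment of effectiveness to GEE, across three time points and adjusted for covariates. The reasons given for GEE are the correlation of repeated measures, low reliance on normality, and estimation over several time points. The university level is not named there.

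Randomization and Blinding makes the university the unit of randomization and has 10 universities to allocate. Study Location speaks of 20. Sample Size expects appreciable clustering: "the average class size is assumed to be 40 participating students, and an ICC of .05 could be expected". From this it derives a design effect of 2.95.

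**The concern.** An ordinary two-sample t or chi-square test takes its standard error from the number of students, as if each had been allocated separately. Here whole universities are allocated, and the plan itself expects students within a university to resemble each other enough to nearly triple the required sample. A test that leaves this out understates the standard error and produces P values that are too small.

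The named tests therefore cannot keep the promise made in the sentence before them. An analyst who follows the text literally would have two between-arm P values for acculturative stress, one from the GEE and one from a t test, with nothing to say that the second carries no weight. If the tests are meant for baseline only, the text does not say so. Unadjusted tests there could also report imbalance more often than their nominal level.

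**Working it through.** **Inputs from the protocol article**
- Two-sided test at 5% (Statistical Analysis).
- Means and SD: "µ1=2.58, µ2=2.07, SD1=1.08, SD2=1.08, n1=24, n2=30", so the difference is 0.51 and the SD 1.08 (Sample Size).
- Cluster size m = 40 and ICC = .05 (Sample Size).
- 10 universities allocated 1:1 (Randomization and Blinding); 20 mentioned in Study Location.
- Analysable sample: "the total sample size required is 209 participants per arm", so 418 in total.

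**Assumption.** The text does not state the power and the formula figure is not shown. I take 80%, because with a two-sided 5% test it returns the plan's 71. The plan calls 71 a total but then uses it per arm, and it is treated as per arm here.

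**Step 1. Reproduce the plan's own figures**
- n per arm = 2 × (1.96 + 0.84)² × 1.08² / 0.51² ≈ 70.4, rounded up to 71.
- Design effect = 1 + (40 − 1) × .05 = 2.95.
- 71 × 2.95 = 209.45 (stated as 209).
- 209 / 0.8 = 261.25 (stated as 261), hence 522 in total.

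The figures reproduce apart from rounding, so the plan does rest on a design effect of 2.95.

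**Step 2. Type I error of a test that omits the design effect**

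The true standard error is √DE times the one that the ordinary test uses, so a nominal two-sided 5% test rejects a true null with probability 2 × [1 − Φ(1.96 / √DE)]. The same expression serves a chi-square test on one degree of freedom.

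- Plan's m = 40: √2.95 = 1.72; 1.96 / 1.72 = 1.14; error = 25.4%.
- 418 analysable students in 10 universities: m = 41.8; DE = 1 + 40.8 × .05 = 3.04; error = 26.1%.
- All 522 students in 10 universities, no attrition: m = 52.2; DE = 3.56; error = 29.9%.

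**Step 3. Simulation check**

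A pooled student-level t test was simulated with 5 universities per arm, ICC .05, no treatment effect and 40,000 runs per setting. It rejected in 25.6% (m = 40), 26.0% (m = 42) and 30.2% (m = 52) of runs. A t test on university means with 8 degrees of freedom rejected in 5.0% to 5.3% of the same runs.

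**Step 4. Range over what is uncertain**

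The ICC is an expectation, and the document gives two numbers of universities. With 418 analysable students:

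| Universities | Students per university | ICC | Design effect | Type I error |
|---|---|---|---|---|
| 10 | 41.8 | .01 | 1.41 | 9.9% |
| 10 | 41.8 | .02 | 1.82 | 14.6% |
| 10 | 41.8 | .05 | 3.04 | 26.1% |
| 10 | 41.8 | .10 | 5.08 | 38.5% |
| 20 | 20.9 | .05 | 2.00 | 16.5% |

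In every row shown, the error is about twice the nominal 5% or more.

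**The case against.** The strongest reply is that the plan does not set out to ignore clustering. It says the reverse in the sentence before the tests. The Results section also promises reporting at cluster and individual level, with an ICC for each outcome. Effectiveness is assigned to GEE, which is also the only method that the abstract names. The sentence on t and chi-square tests states no hypothesis and groups outcomes with sociodemographic variables, so it may describe a table of baseline comparability. That would fit the first two study aims, which concern baseline description. The article is also a condensed account, and details of secondary comparisons may stand elsewhere.

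Much of this stands. A reader might infer that the plan chooses to ignore clustering, or that the trial has a 26% false-positive rate. The document supports neither. The figure belongs to a test run unadjusted and used to judge effect, not to the GEE. A reader might also infer that baseline P values would steer the choice of covariates. The text says only that the GEE is adjusted for covariates, not that they are picked by significance. Nor can the inflation for sociodemographic variables be sized, because no ICC is given for them.

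The mismatch itself remains. A general promise does not alter a named test that has no term for clustering, and no adjusted version is named. The baseline reading is possible but not stated: the sentence includes the primary and secondary outcomes, and the one after it turns to complete-case, intent-to-treat and completer analyses, which bear on follow-up data. This is something the article states, not a detail it leaves out.

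**Conclusion.** The point holds as an internal contradiction in Statistical Analysis. The tests named for between-arm comparison, outcomes included, do not account for clustering, although the section promises that the analysis will and the sample size relies on a design effect of 2.95. Their P values for the outcomes would be invalid if the tests were run as written.

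The size is conditional. Used unadjusted on an outcome, the nominal 5% would become about 25-26% with ICC .05 and 10 universities of 40 to 42 analysable students. It would be about 10% to 38% for ICCs from .01 to .10, and about 17% with 20 universities at ICC .05. These figures do not describe the GEE, whose own error rate is a separate question. The stated effectiveness analysis does not depend on the t and chi-square tests, so the remedy is to the text and not to the design.

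**What to change.** In Statistical Analysis:

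1. Remove the unadjusted t and chi-square comparisons of the primary and secondary outcomes, or replace them with cluster-adjusted tests or tests on university-level summaries.
2. State that every between-arm P value and confidence interval for an outcome comes from the model that accounts for clustering by university, and name the university as a level of that model.
3. Say that baseline characteristics will be presented by arm descriptively. If tests are kept there, state that they apply to baseline and use cluster-adjusted versions.

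The cost is wording only. No change to the sample, data collection or schedule is needed.
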